### Statistical analysis

#### Sample size/power calculation

The power calculation is based on the assumption of 90 % clinical recovery in the reference group and no difference between the two groups. The non-inferiority limit is set to minus 10%, the confidence level (two-sided) to 95 %, the power to 85 % and the distribution between the groups to 1/1. Based on these presumptions, 324 evaluable patients (162 in each group) are needed to be able to demonstrate non-inferiority between treatment groups. Presuming that 25 % of the included patients will not be possible to evaluate 432 (324*(1/0.75)) patients are needed to be included.

All effect variables will be analyzed for per protocol population (PP) as well as for the modified intention to treat (MITT) population as sensitivity analysis.

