There are few published studies comparing 10 days treatment duration with shorter treatment durations with penicillin V. Three studies which were published in the 1980s have been identified. Five versus 10 days (250 mg three times daily and 800 mg twice daily respectively) [9, 10] and 7 versus 10 days (500 mg three times daily) [11] were studied. All of the studies concluded that 10 days of treatment was preferable but in the light of current knowledge of pharmacokinetics and pharmacodynamics (PK/PD) the doses used in these studies were suboptimal. The effect of beta-lactam antibiotics is dependent on time above the minimum inhibitory concentration (MIC) of the unbound drug concentration in serum (free drug time above MIC; fT > MIC). Usually, the target is that 95–99 % of the population should achieve a fT > MIC of around 30–40 % for non-severe infections [12], also expressed as the population target attainment for a given target. For beta-lactams a more frequent dosing is preferred and the dosing interval is more critical than the size of the dose [12]. The dosing regimen 800 mg four times daily provides better target attainment compared to 1000 mg three times daily (33 % fT > MIC compared to 25 % fT > MIC at the breakpoint MIC 0.25 mg/L). Our hypothesis is that the experimental dosage regimen 800 mg four times daily gives at least the same efficacy, possibly better patient adherence and a significantly lower total exposure.

In the present study we will examine if penicillin V given four times daily for 5 days is non-inferior to the currently recommended dose regimen of 10 days to patients with pharyngotonsillitis caused by streptococcus group A. Reducing the treatment duration to 5 days will almost halve the consumption of penicillin V for this indication. A shorter treatment duration may potentially improve patient adherence [13], cause less effect on the human microbiota [14] as well as lower medicinal costs for patients and community.

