#### Intervention

Patients will be randomized to treatment with penicillin V four times daily for 5 days or three times daily for 10 days. The dosages for different weight groups are presented in Table 1.

**Table 1 Tab1:** Penicillin V dosing schedule

Body weight	Dosage 5 days treatment	Dosage 10 days treatment
>40 kg	800 mg × 4	1000 mg × 3
20–40 kg	500 mg × 4	500 mg × 3
10–20 kg	250 mg × 4	250 mg × 3

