#### Secondary outcomes

The secondary outcomes are bacteriological eradication according to the culture taken at the TOC, time to relief of symptoms according to the patient diary, frequency of relapses one month after first diagnosis, frequency of complications during the study period as well as pattern of adverse events.

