## Abbreviations

CRF: Case record form
GAS: Gtreptococcus group A
GCP: Good clinical practice
ICH: International conference on harmonization
MIC: Minimum inhibitory concentration
MITT: Modified intention to treat population. Patients who received at least one dose of the study drug
PHC: Primary health care
PHCC: Primary health care centre
PK/PD: Pharmacokinetics and pharmacodynamics
PP: Per protocol population. Patients without violations to the study protocol, receiving at least 80 % of the prescribed study drug and evaluable at least until the TOC visit.
RADT: Rapid antigen detection test
RCT: Randomized controlled trial
TOC: Test of cure

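### Time to relief of symptoms is led by the per-protocol set, whose 80% intake rule is met at about day 4 in one arm and day 8 in the other, so the lead comparison is not protected by randomization

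*Protocol article*

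**What the plan says.** The only statement on analysis sets is in the Protocol article, Statistical analysis, under Sample size/power calculation: "All effect variables will be analyzed for per protocol population (PP"), with the MITT population added as a sensitivity analysis. It makes no exception for any outcome.

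The Secondary outcomes section lists "time to relief of symptoms according to the patient diary" among the efficacy outcomes.

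The Abbreviations section defines the two sets. PP is "Patients without violations to the study protocol, receiving at least 80 % of the prescribed study drug and evaluable at least until the TOC visit". MITT is "Patients who received at least one dose of the study drug".

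The Intervention section gives the two courses: "Patients will be randomized to treatment with penicillin V four times daily for 5 days or three times daily for 10 days".

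Under Visit one, the diary records tablet intake, sore throat and fever each day and is kept until the follow-up visit. Symptoms and intake therefore come from the same daily record.

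**The concern.** Relief will often come before the end of the course, and a patient who feels well may stop taking tablets. Whether that patient enters the PP set is then decided after the outcome has occurred, and partly because of it. The intake threshold falls twice as late in the 10-day arm. A patient relieved on day 4 who stops after day 6 stays in the PP set if assigned to 5 days and leaves it if assigned to 10. Two groups that were comparable at randomization need not be comparable after this selection.

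The usual reason for leading with PP does not reach this outcome. In a non-inferiority test, non-adherence can hide a real difference, so PP has a recognised place. The limit of minus 10% belongs to clinical cure, and none is stated for time to relief. Nor is 80% intake or a test-of-cure visit needed to see when symptoms ended, since the diary records them daily.

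At stake is a difference in speed of relief that selection alone could produce. If it favoured the 5-day arm, it could be read as support for the hypothesis in the Background section about the four-times-daily regimen.

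**Working it through.** **The plan's own figure.** With 90% cure in both groups, a limit of 10 points, two-sided 95% confidence and 85% power: (1.960 + 1.036)² × 2 × 0.9 × 0.1 / 0.10² = 161.6, so 162 per group and 324 in all; 324 / 0.75 = 432. This reproduces the protocol and is not affected by the point.

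**The 80% threshold by arm** (courses from Intervention, rule from Abbreviations).
- 5-day arm: 4 × 5 = 20 doses; 0.8 × 20 = 16; 16 / 4 per day = 4.0 days.
- 10-day arm: 3 × 10 = 30 doses; 0.8 × 30 = 24; 24 / 3 per day = 8.0 days.

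**One case worked exactly.** Assumptions, not in the documents: the relief day T is geometric with median 3 in both arms, so p = 1 - 0.5^(1/3) = 0.2063 and mean 1/p = 4.85 days. After relief, 5% stop for good each day, and the last tablet day is T + G with G geometric at 5%. A patient is excluded if T + G is 3 or less (5-day arm) or 7 or less (10-day arm).
- Excluded, 5-day arm: 0.2063 × (1 - 0.95²) + 0.1637 × 0.05 = 0.0201 + 0.0082 = 2.8%.
- Excluded, 10-day arm: sum over t = 1 to 6 of P(T = t) × (1 - 0.95^(7-t)) = 0.0547 + 0.0370 + 0.0241 + 0.0147 + 0.0080 + 0.0032 = 14.2%.
- PP mean, 5-day arm: (4.847 - 1 × 0.0201 - 2 × 0.0082) / 0.9717 = 4.95 days.
- PP mean, 10-day arm: (4.847 - 0.319) / 0.8583 = 5.28 days, where 0.319 is the sum of t times the terms above.
- Gap: 0.32 day, with a true difference of zero.
- Relieved by day 3, 5-day arm: (0.5 - 0.0283) / 0.9717 = 48.5%. 10-day arm: (0.5 - 0.1158) / 0.8583 = 44.8%.

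**Other assumed patterns, identical relief in both arms.** Gap is PP mean time to relief, 10-day minus 5-day.

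| Relief time | Stopping after relief | Excluded, 5-day v 10-day | Gap (days) |
|---|---|---|---|
| Geometric, median 2 to 4 (long tail) | 3 to 10% per day | 1-8% v 7-32% | 0.1 to 0.8 |
| Gamma (shape 4), median about 3 to 5 | 10 to 30% of patients stop 1 or 2 days after relief | 0.1-7% v 7-28% | -0.04 to 0.30 |
| Lognormal, log-SD 0.4, median 2 to 4 | 3 to 10% per day | not tabulated | 0.00 to 0.21 |
| Lognormal, median 2 to 5 | 10 to 30% stop within 0 to 2 days | more lost in the 10-day arm throughout | -0.14 to 0.38 |

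The negative values arise when relief is fast and stopping almost immediate: the 5-day arm then also loses its fastest recoverers. In the third row the PP medians were the same in both arms in every scenario.

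**Plausibility of the top value.** The 0.8 day comes from the geometric model with median 4 and 10% stopping per day. That model leaves 0.5^(10/4) = 17.7% unrelieved at day 10 and 0.5^(12/4) = 12.5% at day 12. The 5-day arm's test-of-cure visit falls at days 10 to 12 (5 + 5 to 5 + 7), and the protocol assumes 90% cured with no residual symptoms. The case does not fit that assumption. Median 3 does fit (0.5^(10/3) = 9.9% at day 10), and the same formulae at 10% stopping per day give 5.06 v 5.74 days, a gap of 0.68. In these patterns, gaps above about 0.4 day arise only with the long-tailed geometric form.

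**Against sampling error.** For the worked case the SD of T is √(1 - p)/p = 4.32 days. With 162 per arm the standard error of the difference is 4.32 × √(2/162) = 0.48 day, larger than the gap of 0.32.

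**The case against.** The strongest reply is that the remedy is already in the plan. Every effect variable is also analysed in MITT, which keeps everyone with at least one dose, so a selection effect confined to PP would show as a discrepancy between the two results. The article is also a condensed account, and outcome-specific analysis sets may be settled in a document not shown. The first part is true, but it does not say which result leads when the two differ, and the article ranks the less selected set second. On the second part, the article does not leave the choice open: it fixes it, for all effect variables.

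The objections to size and direction do stand, and they limit what can be claimed.
- A reader might infer that the rule makes the 5-day regimen look faster. The documents do not support that as a certainty: the sign depends on how soon after relief patients stop.
- A reader might take 0.8 day as the expected bias. It comes from one tail shape and conflicts with the protocol's own cure assumption.
- A reader might take the remarks in Background and Discussion, for example "A shorter treatment duration may potentially improve patient adherence", as evidence of early stopping. They are hopes about adherence. They give no rate and no link to relief.
- The models cover only permanent stopping after relief. Scattered missed doses, possibly more frequent with four daily doses, could remove patients from the 5-day arm instead.
- Nothing here shows that leading with PP is wrong for the non-inferiority primary outcome.

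**Conclusion.** The point holds as a stated analysis choice that fits this outcome badly. The 4-day and 8-day thresholds and the rank of PP above MITT follow directly from the article. That early stoppers are lost more often from the 10-day arm follows once some patients stop after feeling well, which is an assumption, though an ordinary one.

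The size is unknown. With identical arms, the assumed patterns give a spurious gap from about -0.1 day, through 0.0 to 0.4 day in most scenarios, to about 0.8 day in the long-tailed extreme. The gap may well be below sampling error at 162 per arm. It usually favours the 5-day regimen.

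Importance is minor to moderate: one secondary outcome is affected, and neither the primary comparison nor the sample size is touched.

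**What to change.** Add one sentence after the statement on analysis sets under Sample size/power calculation: for time to relief of symptoms, the lead analysis uses the MITT set (all treated patients with diary data, whatever their later intake or test-of-cure attendance), with PP as the sensitivity analysis. The order for the primary outcome need not change.

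The cost is that sentence. Both analyses are planned and the diary data are collected, so no patients, visits or measurements are added. The trade-off is a lead estimate that includes non-adherent patients and so describes relief under the assigned regimen as actually taken. One limit remains: the article does not say how diaries are returned. If they come back only at the test-of-cure visit, patients who miss it may still lack data, and the number without a diary should be reported by arm.

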#### Visit one

Patients presenting with sore throat will be clinically examined by a physician. In case of suspected faryngotonsillitis and 3–4 Centor criteria a RADT for GAS will be performed. Patients with a positive RADT test for GAS who meet all the inclusion criteria, and none of the exclusion criteria, will be asked to participate in the trial. After signed informed consent, by patient or guardian, the patient will be asked about medical history, demographic data, previous antibiotic exposure and concomitant drug treatment.

A throat swab for semi quantitative cultures of streptococcus group A, C and G will be performed.

After randomization to intervention group 5 or 10 days the physician prescribes penicillin V which the patient will retrieve from the pharmacy. A patient diary is handed out which the patient or guardian is asked to fill in until the follow-up visit, five to seven days after treatment discontinuation.

Demographic data and clinical data will be recorded in a case report form (CRF) by study personnel. In addition, data regarding intake of penicillin V doses and analgesics, presence of sore throat and fever, adverse events etc. is filled in daily by each patient or guardian in the diary.

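### The per-protocol set alone decides non-inferiority in this open-label trial; both analysis sets should have to agree

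*Protocol article*

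**What the plan says.** Under Sample size/power calculation, the protocol article analyses all effect variables in PP, "as well as for the modified intention to treat (MITT) population as sensitivity analysis". The margin is given there too: "The non-inferiority limit is set to minus 10" percent, with a two-sided 95% confidence level. The power of 85% is computed on 324 evaluable patients out of 432 included, because 25% "of the included patients will not be possible to evaluate".

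The Abbreviations define the sets. PP needs no protocol violation, at least 80% of the prescribed drug, and evaluability to the TOC visit. MITT is "Patients who received at least one dose of the study drug".

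The Design section states that the trial is open-label. According to Visit one, after randomisation "the physician prescribes penicillin V which the patient will retrieve from the pharmacy". The Background hypothesis for the 5-day regimen includes "possibly better patient adherence", and the Ethical issues section repeats, again tentatively, that adherence may improve. Table 3 limits the term not evaluable to missing follow-up.

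**The concern.** The text ranks the two sets. MITT is labelled a sensitivity analysis and the sample size is built on evaluable patients, so PP carries the conclusion. Nothing stated requires MITT to support it.

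Membership of PP is settled after randomisation, by patients and physicians who know the allocation. The 80% rule also acts at different times in the two arms. A patient who takes every dose and stops at the end of day 5, 6 or 7 stays in PP in the 5-day arm and is dropped in the 10-day arm. A PP comparison is then no longer between randomised groups, and any practical benefit of better adherence is conditioned away.

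MITT does not fully restore the randomised comparison either. It requires a first dose, and the patient learns the allocation before collecting the drug.

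At stake is the main claim of a trial meant to inform treatment duration. A PP success that the randomised groups contradict would not be credible, and the stated ranking allows it.

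**Working it through.** **1. The plan's own figure.** Inputs from Sample size/power calculation: cure 90% in both arms, margin 10 points, one-sided 0.025, power 85%, allocation 1:1.

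n per arm = (1.960 + 1.036)² × 2 × 0.90 × 0.10 / 0.10² = 161.6, so 162 per arm and 324 in total. Then 324 / 0.75 = 432, or 216 per arm. Both figures reproduce. Power at 162 per arm is 85.1%. The sample size is correct for PP.

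**2. The adherence threshold by arm.** Regimens from Table 1, threshold from the Abbreviations.
- 5-day arm: 4 × 5 = 20 doses; 80% = 16 doses = 4 full days.
- 10-day arm: 3 × 10 = 30 doses; 80% = 24 doses = 8 full days.

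**3. What PP could hide.** Take PP cure as 90% in both arms, so the PP difference is 0. Exclusion shares and cure among the excluded are assumptions; the documents give neither by arm. All-patient cure = (1 − x) × 0.90 + x × e, where x is the share excluded and e the cure rate among them.

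| Excluded, 10-day / 5-day | Cure among excluded, 10-day / 5-day | All-patient difference (5-day minus 10-day) |
|---|---|---|
| 30% / 20% | 50% / 50% | 0.82 − 0.78 = +4 points |
| 30% / 20% | 70% / 70% | 0.86 − 0.84 = +2 points |
| 20% / 30% | 50–70% in both | −4 to −2 points |
| 25% / 25% | 90% / 70% | 0.25 × (0.70 − 0.90) = −5.0 points |
| 25% / 25% | 90% / 60% | 0.25 × (0.60 − 0.90) = −7.5 points |

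The shift can be a material part of the margin, in either direction. The last two rows follow directly from the assumed inputs and show only what is possible.

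**4. Power of a rule that needs both sets.** Simulation with 216 per arm, no true difference, PP cure 90%, and unpooled 95% limits (200,000 trials per scenario). Assumed: 10% or 15% have no TOC outcome, and the rest of the 25% (15 or 10 points) have a TOC outcome but fall outside PP. They make up 15/90 = 16.7% or 10/85 = 11.8% of observed patients. The second set is all randomised patients with an observed TOC outcome.

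| Cure outside PP (both arms) | PP alone | Observed set alone (10% / 15% missing) | Both (10% / 15% missing) |
|---|---|---|---|
| 90% | 85% | 90.7% / 89.0% | 83.8% / 83.7% |
| 80% | 85% | 86.7% / 86.0% | 80.9% / 81.3% |
| 70% | 85% | 82.7% / 83.1% | 77.8% / 78.9% |

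If the second set were instead everyone randomised, with missing TOC counted as failure, joint power at 90% cure would be 70.5% with 10% missing and 64.7% with 15%.

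**The case against.** PP as the main set is customary in non-inferiority trials, because intention-to-treat sets can dilute a real difference. The protocol also commits to reporting both sets, so a conflict would be visible. How to read a conflict, and how to treat missing TOC outcomes, may be laid out in the full protocol or the analysis plan. Much of this stands: using PP is not a fault, and missing-data handling is not counted against the article. But the ranking of the sets is stated here, and it leaves PP decisive.

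A reader might infer more than the documents support:
- *That PP favours the 5-day arm.* The direction is unknown. If adherence is worse over 10 days and poor adherers do worse, PP removes a 5-day advantage and is conservative (first two rows of the first table). Nothing supports worse outcomes specifically among excluded 5-day patients.
- *That the plan predicts an adherence difference.* It says "possibly better patient adherence"; the wording is tentative throughout.
- *That at most a quarter of patients leave PP.* The 25% is a planning presumption about patients who cannot be evaluated. Table 3 ties that term to missing follow-up, while PP also drops low adherers and violators. It is neither a ceiling nor a measure of PP exclusions. Patients without follow-up have no observed outcome in MITT either, so a change of set does not bring them back.
- *That the first-dose condition removes many patients.* No figure is given for patients who never start.

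**Conclusion.** The point holds as a weakness in the stated decision rule, not as a demonstrated bias. Non-inferiority can rest on a set selected by post-randomisation adherence in an open-label trial, with the other set unable to overturn it. Under the assumed scenarios the hidden difference is some 2 to 7.5 points against a 10-point margin, of unknown sign.

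Requiring both sets costs about 1 to 8 points of power: from 85% to about 84% if observed patients outside PP are cured at 90%, about 81% at 80%, and about 77–79% at 70%. It would be tempting to say that power stays at about 84% for all randomised patients. That holds only for observed outcomes with 90% cure outside PP. Counting missing TOC as failure brings it to about 65–70%. All these figures assume no true difference and 10–15% missing TOC outcomes.

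**What to change.** Make the two sets co-primary by replacing the sensitivity-analysis wording with:

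> Non-inferiority is concluded only if the lower limit of the two-sided 95% CI exceeds −10 percentage points in both the PP population and the intention-to-treat population (all randomised patients with an observed TOC outcome, in their allocated arm, without the first-dose condition).

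Keep analyses that impute missing TOC outcomes as sensitivity analyses. Restate power for the joint rule as a range with its assumptions: about 84%, 81% and 77–79% for 90%, 80% and 70% cure among observed patients outside PP, against 85% for PP alone.

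Cost: a change of wording and about 1 to 8 points of power. No extra patients or data are needed, and no alpha adjustment, because both tests must succeed.

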#### Safety

Patterns of adverse events between the two treatment groups will be evaluated and analysed descriptively. Active surveillance of adverse events will be done by a physician at TOC and by self-reporting by the patient/guardian in the patient diary. At the follow-up controls 1 and 3 months after discontinuation of treatment, patients will be asked about adverse events that are still ongoing at the previous visit.

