### Context and procedure

Study procedures are presented in Table 2.

**Table 2 Tab2:** Study procedures for both intervention groups, penicillin V given four times daily for 5 days or three times daily for 10 days

	Baseline	5–7 days after penicillin V treatment discontinuation.	1 month (by telephone)	3 months (by telephone)
Clinical judgement by physician	X	X		
Anamnesis	X			
Written informed consent	X			
Inclusion/exclusion criteria	X			
Concomitant drug treatment	X	X		
Rapid antigen detection test (RADT)	X	X		
Throat swab culture	X	X		
Evaluation of primary endpoint		X		
Monitoring adverse events		X	X^a^	
Monitoring relapses		X	X	
Monitoring complications			X	X

^a^Follow-up of adverse events which were ongoing at previous contact

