#### Test-of-cure visit

A test-of cure (TOC) visit will be performed at the PHCC 5 to 7 days after completion of antibiotic treatment. Clinical judgement of throat status, a new RADT and culture, and recording of adverse events will be performed.

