#### Ethical issues

It is important to include children in clinical trials, especially since children often suffer from infections and therefore are treated with antibiotics more often than other age groups. The lower age limit 6 years was chosen based on presumed ability to swallow tablets, since exposure is easier to control with tablets than with oral suspension.

We consider that there are no risks to participate in the study, regardless of age. The sampling is simple and follow the normal routines at the PHCCs. Both treatment alternatives are expected to be effective against the infection. A shorter treatment regimen could include benefits in form of less adverse events and less disturbances in the human microbiota. In addition, patient adherence to the treatment may improve with shorter treatment duration.

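### New adverse events are collected only to the test-of-cure visit, about day 11 in the 5-day arm and day 16 in the 10-day arm, which tilts a crude comparison towards the shorter course

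*Protocol article*

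**What the plan says.** All references are to the protocol article.

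- Intervention: "Patients will be randomized to treatment with penicillin V four times daily for 5 days or three times daily for 10 days".
- Test-of-cure visit: the "visit will be performed at the PHCC 5 to 7 days after completion of antibiotic treatment". The visit is thus timed from the end of treatment, not from randomisation.
- Safety, up to TOC: "Active surveillance of adverse events will be done by a physician at TOC and by self-reporting by the patient/guardian in the patient diary". Under Visit one, the diary is completed daily, includes adverse events, and is "asked to fill in until the follow-up visit, five to seven days after treatment discontinuation".
- Safety, after TOC: at the 1- and 3-month contacts "patients will be asked about adverse events that are still ongoing at the previous visit". Follow-up controls gives the same restriction, and footnote a of Table 2 reads "Follow-up of adverse events which were ongoing at previous contact".
- Secondary outcomes lists the pattern of adverse events. Safety says that the groups will be compared descriptively.
- Ethical issues: "A shorter treatment regimen could include benefits in form of less adverse events".

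Table 2 marks adverse-event monitoring at TOC and 1 month only, whereas Follow-up controls and Safety follow ongoing events at both 1 and 3 months.

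**The concern.** The period in which a new adverse event can enter the data ends on a different day in each arm, because treatment length differs by five days and TOC is tied to the last dose. No later contact asks about new events. A patient in the 10-day arm who develops a new complaint on day 14 is asked about it. A patient in the 5-day arm with the same complaint on the same day has normally handed in the diary and had the last contact that asks for new events.

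The pattern of adverse events is a named secondary outcome, and the article mentions fewer events as a possible benefit of the short course. The Discussion also allows that its higher daily dose may raise the risk of adverse events. Shorter observation in that arm favours the hoped-for result and could hide part of the risk that the authors raise. The rule concerns data collection, so an analysis plan can choose the window but cannot recover events that nobody asked about.

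**Working it through.** The plan states no adverse-event rate and no window length, so it has no figure of its own to reproduce on this point.

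**1. Length of observation for new events** (Intervention; Test-of-cure visit; Visit one; Safety). Last observed day = treatment days + TOC offset.
- 5-day arm: 5 + 5 to 5 + 7 = day 10-12, midpoint 11.
- 10-day arm: 10 + 5 to 10 + 7 = day 15-17, midpoint 16.
- Ratio at the same offset: 15/10 = 1.50; 16/11 = 1.45; 17/12 = 1.42. The 10-day arm is observed 42-50% longer.
- Pairing opposite ends of the visit window gives 15/12 = 1.25 to 17/10 = 1.70, but randomised arms would not be expected to differ that way.

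**2. What is lost.** Table 2 monitors relapses at TOC and 1 month, and complications at 1 and 3 months. The loss is therefore confined to new events of other kinds. After about day 16 neither arm is asked about these, so the asymmetry sits in about days 11-16.

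**3. Illustration with no drug effect.** Assume the same daily onset probability r in both arms, on and off drug. Share with at least one event by TOC = 1 - (1 - r)^days, with 11 and 16 days:
- r = 1%: 1 - 0.99^11 = 10.5% v 1 - 0.99^16 = 14.9% (4.4 points).
- r = 2%: 19.9% v 27.6% (7.7 points).
- r = 3%: 28.5% v 38.6% (10.1 points).

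Under this assumption the whole gap is artefact, and over a common 16 days it would be zero.

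**4. Illustration with a drug effect.** Assume a hazard of 0.03 per day on drug and 0.01 per day off drug.
- 5-day arm to TOC: 1 - exp(-(5 × 0.03 + 6 × 0.01)) = 1 - exp(-0.21) = 18.9%.
- 10-day arm to TOC: 1 - exp(-(10 × 0.03 + 6 × 0.01)) = 1 - exp(-0.36) = 30.2%.
- 5-day arm to day 16: 1 - exp(-(5 × 0.03 + 11 × 0.01)) = 1 - exp(-0.26) = 22.9%.
- Gap to TOC 11.3 points; gap over a common 16 days 7.3 points; artefact about 4 points.

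With an off-drug hazard of zero, the gap to TOC and the gap to day 16 are both 12.0 points and the artefact is nil.

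**5. Can the 1-month call close the gap?** Follow-up controls places it 28-35 days after the last treatment day: day 33-40 in the 5-day arm (5 + 28 to 5 + 35) and day 38-45 in the 10-day arm (10 + 28 to 10 + 35). Day 30 lies before both ranges, so days 1-30 can be covered in each arm.

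**The case against.** The best defence is that each arm is followed for its treatment period plus the same 5-7 days. That is a symmetric on-treatment-plus-washout window, and events caused by treatment days 6-10 should count against the longer course. This stands, and it limits the point. A reader might infer that the plan builds in a false safety advantage equal to the whole between-arm gap. The documents do not support that: the gap is pure artefact only if onset is equally likely on and off drug, and nothing in the article says so.

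A reader might also infer that late events in the 5-day arm are never recorded. That too is broader than the text, since relapses and complications are still monitored after TOC, and other new events after about day 16 go unasked in both arms.

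The comparison is descriptive, so no test, margin or error rate is affected. The article says only that fewer events could be a benefit; its hypothesis names efficacy, adherence and exposure.

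Finally, the choice of analysis window and the use of person-days can be left to an analysis plan that is not shown. That is fair, but the absence of any question about new events after TOC is a stated collection rule and remains.

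**Conclusion.** The point holds as a modest, inexpensive improvement. The window lengths (about 11 v 16 days) and the direction of the tilt follow directly from the text. The size does not: it depends on how often new events other than relapses and complications start on about days 11-16 in patients who stopped treatment on day 5, and the article gives no rate. The figures of 10.5% v 14.9% assume a constant 1% per day regardless of exposure. They are an upper-end illustration in the sense that the whole gap is then artefact, and they are not a forecast. If almost no events start that late after a short course, the artefact is near zero.

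The primary outcome is untouched. What is at risk is the reading of a crude to-TOC table as evidence that the short course causes fewer adverse events.

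The disagreement between Table 2 and the text on the 3-month call is certain but clerical. Neither version collects new events after TOC.

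**What to change.** - In the 1-month call already planned, ask both arms about any new adverse event since TOC and record its onset date.
- Compare the arms over a common window from randomisation, for example days 1-30.
- Show the to-TOC table alongside, with person-days of observation in each arm.
- Show a day 1-10 table from the diaries only as a sensitivity analysis. It uses the same method in both arms but leaves the 10-day arm with no post-treatment time, so it should not be the main comparison.
- Reconcile Table 2 with Follow-up controls and Safety on whether ongoing events are followed at 3 months.

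Cost: one extra case report form question, slightly longer calls and some analysis-plan wording; no added visit. The remedy is imperfect. Days 12-16 would rest on telephone recall in the 5-day arm but on the diary in the 10-day arm, so some under-reporting in the 5-day arm may remain and should be stated with the results.
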